### Analysis and data processing

#### The questionnaire

Descriptive statistics will be used for assessing demographic characteristics and self-reported functional health status (COOP-WONCA). For assessing self-reported levels of different communication aspects (QUOTE-COMM), e.g., before, after and at follow-up, descriptive and inferential statistics will be used.

#### Audio recordings

For analysis of patient involvement, ARs will be coded with the OPTION^5^ scale, a reliable and valid instrument for investigating patient involvement in decision-making [36, 37]. Coding of ARs using OPTION^5^ allows for the assessment of the extent to which RNs involve patients in decision-making. Five items are coded on a 5-point Likert scale, from 0 = ‘zero effort observed’ to 4 = ‘exemplary effort’. The total score is generated by converting the scores to a 0–100 scale and then calculating the average. The higher the score is, the higher the level of patient involvement.

For analysis of patient-RN communication on patients’ expressions on health concerns and RNs’ responses to these concerns, ARs will be coded with the Verona Coding Definitions on Emotional Sequences (VR-CoDES) [38, 39]. The coding identifies episodes and sequences of negative emotions, e.g., elicitations and expressions of patients’ cues and concerns, and RNs’ responses. The VR-CoDES allows for analysis of communication strategies used by RNs to respond to and explore health concerns and needs. When using the VR-CoDES, data are processed and coded directly from the recordings, and transcriptions are not needed. The data will allow for both statistical and qualitative analysis. Descriptive statistics will be used to describe and explore the frequencies and types of health concerns of patients’ concerns and RNs’ responses. The characteristics of emotional sequences of communication and the distribution of categories will be described. In conformity with the data level and distribution, parametric or non-parametric tests will be used for analysis of possible differences between patients’ expressions versus RNs’ responses and sex. There will also be a qualitative analysis of patterns in these sequences related to RNs’ responses and questions used to understand communication strategies efficient for RNs’ exploration and assessment of patients’ health concerns. For statistical analysis, the necessity of performing multilevel analysis will be considered by calculating intraclass correlation coefficients given the nested data structure of consultations and the clustering of data.

For all statistical analyses, SPSS Statistics for Windows, latest version, will be used. The coding with OPTION^5^ and VR-CoDES will be performed by two independent coders, and the inter-rater reliability between them will be checked using Cohen’s kappa [43, 44].

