### Recruitment procedure

The study aims to collect a purposive sample of 150 patient-RN consultations, including 30 RNs and 150 patients, distributed among the RNs. Patients and RNs will be recruited at primary care centers in three geographic areas of southwest Sweden to include primary care centers in both urban and rural areas and both public and private (under contract) providers. To facilitate recruitment of participants, some of the researchers will act as local contact persons. Initially, RNs will be informed and recruited. Afterwards, the local contact person will be on site to recruit potential patients to minimize the impact on ordinary care work.

First, we will approach eligible RNs. Three researchers, one in each area, will inform RNs about the research and ask for participation. RNs will be recruited after informed consent. Eligible adult patients (aged 18 years or older) with an appointment to the participating RNs during preselected study days will be informed about the research and invited to participate by one of the researchers. Patients who are willing to participate will be asked to give written informed consent.

To assess patient-reported outcomes, patients will be asked to complete a questionnaire before and after the consultation and at the two-week follow-up (specific aim 1). To monitor communication during patient-RN visits, audio-recordings of communication during these consultations will be made (specific aim 2). To investigate RNs’ clinical reasoning, assessments made, and priorities or related value conflicts, reflective interviews individually and in focus groups will be conducted (specific aim 3). Data will be collected in 2023 and 2024 and analyzed and reported from 2023 to 2026. For an overview of the participants and data collection, see Fig. 1. The data gathered and results will be used to disentangle working mechanisms using the realist evaluation methodology [31]. This will aid in the development and design of methodologies for working processes that facilitate efficient and person-centered assessments and decision-making for the management and priority of patients in primary care by RNs (specific aims 4 and 5).

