### Study size

In conformity with the explorative design, a sample size calculation was not performed, as we did not focus on a single outcome to base our power calculation on in this multiple outcome prospective study. Considering the lack of research in this area, the number of observations of patient-RN consultations was deemed sufficient and feasible, and 5 consultations per RN was considered sufficient to determine their communication style. The number of RNs was also chosen considering that a sample size of 30 can be enough to trust the confidence interval. A two-sided α of 0.05 and 95% power will be considered in the data analysis comparing patient and RN age, sex, and educational level.

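### Whether clustering within nurses is modelled depends on a calculated ICC with no stated criterion, although the design fixes the nesting and 30 nurses with 5 consultations each estimate an ICC poorly

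*Protocol article*

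**What the plan says.** Under Recruitment procedure, the protocol article plans "a purposive sample of 150 patient-RN consultations, including 30 RNs and 150 patients, distributed among the RNs". Under Study size it adds that "5 consultations per RN was considered sufficient to determine their communication style", so the design is 30 RNs with 5 consultations each. The same section announces comparisons by patient and RN characteristics: "A two-sided α of 0.05 and 95% power will be considered in the data analysis comparing patient and RN age, sex, and educational level". It also explains that "a sample size calculation was not performed", because the study is explorative and has several outcomes.

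Under Audio recordings, the emotional sequences coded with VR-CoDES are to be tested as follows: "parametric or non-parametric tests will be used for analysis of possible differences between patients’ expressions versus RNs’ responses and sex". The article does not say whether the unit of these tests is the sequence, the consultation or the RN. The paragraph ends with the only provision for clustering: "the necessity of performing multilevel analysis will be considered by calculating intraclass correlation coefficients given the nested data structure of consultations". The sentence goes on to mention the clustering of the data but gives no cut-off, test or fallback model.

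Under The questionnaire, for the QUOTE-COMM scales the article says only that "descriptive and inferential statistics will be used".

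**The concern.** The nesting is not something to be discovered in the data. The design puts five patients under each RN. The statement that five consultations are enough to establish an RN's communication style presupposes that consultations of one RN resemble each other, which means an ICC above zero. VR-CoDES can add a further level, because one consultation can yield several sequences.

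Letting a calculated ICC decide whether this structure is modelled is a preliminary test on a quantity that 30 clusters of 5 estimate imprecisely. Because no criterion is stated, the choice of model can also be made after the results are seen. If the choice falls on an unadjusted analysis while the true ICC is positive, standard errors are too small for overall means and for comparisons between RNs by age, sex or education. Chance findings could then be reported as features of good communication practice.

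**Working it through.** **Inputs from the article:** 30 RNs, m = 5 consultations per RN, two-sided α of 0.05. The one design figure that can be reproduced is 30 x 5 = 150 consultations, and it agrees. There is no power-based sample size to reproduce.

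**Assumed, because the article gives no values:** RN-level ICC of 0.05, 0.10 and 0.20. For sequences, k = 3 to 5 per consultation, RN ICC 0.05 to 0.1 and consultation ICC 0.1 to 0.2.

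**1. How well 30 x 5 detects an ICC.** The one-way ANOVA F-test has 29 and 120 degrees of freedom, with a 5% critical value of 1.562. Under a true ICC, F is inflated by 1 + 5·ICC/(1 − ICC), which is 1.263, 1.556 and 2.25. Power is therefore 21%, 47% and 87% at ICC 0.05, 0.10 and 0.20. A non-significant result is weak evidence of independence at the two lower values.

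**2. Nesting ignored, one value per consultation.** The design effect is DE = 1 + (m − 1)·ICC. Type I error for an RN-level contrast is 2(1 − Φ(1.96/√DE)). Coverage of a nominal 95% interval for an overall mean is one minus that value. Relative interval width is 1/√DE.

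| ICC | DE | Effective N = 150/DE | Relative width | Coverage | Type I error |
|---|---|---|---|---|---|
| 0.05 | 1.2 | 125 | 0.91 | 92.6% | 7.4% |
| 0.10 | 1.4 | 107 | 0.85 | 90.2% | 9.8% |
| 0.20 | 1.8 | 83 | 0.75 | 85.6% | 14.4% |

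Two independent simulations (15 against 15 RNs in the one whose grouping is recorded) agree: unadjusted type I error was 7.3 to 7.5%, 9.3 to 9.6% and 14.2 to 14.7%. A test on RN means held 4.8 to 5.1%.

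**3. The conditional route itself, same design.** If RN is modelled only when the F-test is significant, simulated type I error for an RN-level factor is 6.4%, 6.4% and 5.6% at the three ICCs (5.8%, 6.0% and 5.3% in the other simulation). With a rule of estimated ICC above 0.05 it is 5.4%, 5.1% and 5.1%. Coverage for an overall mean is 93.9%, 93.3% and 94.4% under the F-test rule, and 94.9%, 94.6% and 95.0% under the ICC rule.

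**4. Patient-level factor varying at random within RNs, one value per consultation.** Unadjusted type I error is 4.8 to 5.3%, so there is essentially no problem here.

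**5. Sequences as the unit, all nesting ignored.**

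- RN-level factor: DE = 1 + (k − 1)(ICC_RN + ICC_cons) + 4k·ICC_RN.
  - Lower end: 1 + 2(0.15) + 12(0.05) = 1.9, type I error 15.5%.
  - Upper end: 1 + 4(0.3) + 20(0.1) = 4.2, type I error 33.9%.
- Patient-level factor varying at random within RNs: the last term drops out.
  - Lower end: DE = 1.3, type I error 8.6%.
  - Upper end: DE = 2.2, type I error 18.6%.

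Simulation of the two ends gave 15% and 34% for the RN-level factor, and 8.6% and 18.8% for the patient-level factor.

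**The case against.** The plan does not overlook clustering: it names the nesting and commits to calculating ICCs. The harm from the rule as stated is small at consultation level, as step 3 shows. Even the F-test is an assumed criterion, since the article names none. The worst coverage in the table, 86%, occurs at an ICC of 0.20, where an F-test would miss the clustering in only about 13% of studies. All of this stands, and it limits the size of the problem.

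Three stronger readings are tempting.

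- **That intervals and tests will be too narrow in general.** This needs a positive ICC and a decision not to adjust. It does not extend to patient-level factors with one value per consultation.
- **That the questionnaires are excluded from any clustering provision.** The conditional sentence stands under Audio recordings but opens by referring to statistical analysis in general, so it may cover them. The brief wording on QUOTE-COMM may also be completed in a full protocol or SAP that is not shown.
- **That the VR-CoDES tests will count each sequence as independent.** The article fixes no unit and says that tests follow the level and distribution of the data. It also does not say whose sex is compared, so the figures for RN-level factors cannot be applied to every planned test.

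The objection does not remove the core. A rule without a criterion permits the unadjusted analysis, and the data can say little about whether that choice is safe.

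**Conclusion.** The point holds in limited form. The article fixes badly how nesting is handled: a known design feature is modelled only if an imprecise estimate, judged by no stated standard, suggests it. At consultation level the cost ranges from small, about 5 to 6% type I error if an ICC check is really applied, to about 7%, 10% and 14 to 15% for RN-level factors if clustering is ignored at ICC 0.05, 0.10 and 0.20. The cost is largest, 15 to 34% for RN-level and 8 to 19% for patient-level factors, only if sequences are the unit and nesting is ignored. All these figures rest on assumed ICCs and, for the last, on an assumed number of sequences.

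Severity is moderate. The study is exploratory, has no single primary outcome, and supports its conclusions partly with qualitative analysis.

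**What to change.** Replace the conditional sentence under Audio recordings with a statement that applies to all data sources, for example: All inferential analyses of patient and consultation data, including the questionnaires, account for RN by a random intercept, with an added consultation intercept when emotional sequences are the unit of analysis. A small-sample method suited to 30 clusters (such as Satterthwaite degrees of freedom) is used. ICCs are reported descriptively and do not determine the model.

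The unit of analysis for the VR-CoDES tests should be named in the same place, and it should be said whether sex there means the patient's or the RN's.

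The cost is wording, slightly more analysis work, and slightly wider intervals when the ICC is near zero. SPSS, which the article already names, can fit these models (MIXED and GENLINMIXED). Recruitment and data collection are unaffected.

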#### Interviews

To explore RNs’ experiences of health assessments, clinical reasoning and priorities, a method for thematic analysis of meanings based on descriptive phenomenology will be used [45]. The analysis will focus on individual RNs’ clinical reasoning and priority, how they engage in these processes, and on sense-making and meanings that emerge in their descriptions. The analysis involves a rigorous process where details and aspects of meanings are explored.

Findings from individual interviews on health assessments and clinical reasoning will be summarized in a short text to use as a facilitator for focus groups. Transcripts of the focus groups will be analyzed with thematic analysis [45]. Themes will be qualitatively derived from an inductive meaning-oriented analysis. Co-coding of interviews will be performed to meet quality criteria for qualitative analysis according to the COREQ guidelines [46].

#### Realist evaluation

Using a realist evaluation (what works for whom in what context), we will disentangle the working mechanisms behind good RN-patient communication practices. We do this by looking for CMO configurations, where C stands for Context (the first point of contact visits in primary care with an RN), M for mechanisms (the parts of the communication process, assessments, and decision-making under study) and O for Outcomes (e.g., meeting patients’ expectations and needs and optimal shared decision-making) [31].

#### Ethical considerations

This research was approved by The Swedish Ethical Review Authority (Dnr Ö24-2023/3.1). We do not anticipate any major risk for the participants in the context of this study. Informed written consent will be obtained from all participants in addition to information about the right to withdraw at any time without consequences. The sampling of participants and data storage, flow, and access will be outlined following legislation and safety routines to safeguard the security, privacy, and confidentiality of participants. All participants will be given information about the study, including how personal data will be processed and about the rights to request information on personal information. Through data management, we will securely organize the data to be available for the researchers involved but inaccessible to unauthorized people. A secure backup of data will be used. Reporting of findings will take place in journals, clinics, professionals and conferences. Research publications and data dissemination will not include identifiable data.

## Time plan and realisation

This research is distributed over four years (2023–2027). The recruitment of participants started in August 2023, and the recruitment and data collection of patient-RN consultations is estimated to take approximately 12 months. These data will be analyzed and reported during 2024 and 2025. The interviews and focus groups will be conducted in 2023 and 2024 to be analyzed and reported between 2024 and 2026.

For realization of the proposed research, an approach involving co-creation and collaboration among practitioners is applied. This means that researchers work in close collaboration with practitioners because they are not only important to facilitate researchers’ access to practices but also because they add value to the scope and focus of research questions, study processes, and the depth and interpretation of the findings. Seminars and workshops will be arranged to stimulate co-creation, validate discussions and ensure the integration of experiences and perspectives from RNs’ practices. Collaboration and co-creation with practitioners from different settings is beneficial for knowledge transfer and learning among researchers and RNs. This is also imperative for research findings to be applied and implemented in clinical practices. This research can generate knowledge applicable for the future development of healthcare provision at the local level.

## Discussion

This research can contribute to the knowledge needed for the guidance of first-line decision-making processes to best meet patient and public health needs. This knowledge is necessary for the development of assessments and decisions to be better aligned to patients and to set priorities. Insights from the research can empower patients and service providers and help understand communication strategies feasible for person-centered care and to support patient health literacy. According to a recent review about RN-patient communication [25], there is an urgent need for in-depth research in this area, especially with the transformation of secondary healthcare to primary care.

The providers’ self-reported ratings of communication skills, empathy, mindfulness and emotional intelligence will give a broad description of traits known to impact communication in healthcare settings. The combination of data from the observational analysis of the visits, rating scales and questionnaires can provide indications of the traits of the healthcare provider that are important to facilitate person-centered communication.

We believe that if assessment processes are optimized properly, RNs can manage uncomplicated acute conditions and illnesses and then free up physicians to more complex patients and how to better meet patients’ demand for help and support. Consequently, this research will contribute to improving primary care services for patients.

A strength of this research is the data collected on real-time communication observed with ARs from patient-RN consultations in its natural context. Naturalistic observations by recordings allow researchers to observe communication between patients and RNs directly in the environment where it occurs in this study without the researcher interacting with participants [47]. The ecological validity in observational studies is considered high.

An important strength of this research is that both patients’ and RNs’ perspectives are in focus combined with data from observed visits, questionnaires and interviews. This will generate rich data that will allow for broad descriptions important for communication and decision-making during RNs’ initial assessment of patients’ health problems in primary care. However, some limitations are worth nothing. First, a constraint of this research may be the use of ARs instead of video recordings. This methodological decision restricts the analysis exclusively to verbal communication, precluding the analysis of nonverbal communication. However, it is worth mentioning that there exists a high correlation between the observations of ARs and video-recordings [48]. The choice of using ARs is based on practical reasons. It is easy to use and may have less impact on ordinary care work and less intrusion into participants’ integrity compared with video recordings [47], even though ARs could also be perceived as sensitive and uncomfortable. In this research, we will perform observations to study communication because of its advantages. At the same time, there is a potential risk that the participants will change their behavior or that the observations will disturb the usual practice. Second, additional challenges might arise from conducting stimulated recall with RNs due to a potential concern that RNs feel questioned about their communication and assessment during the observed visits. This could result in the tendency to formulate post-hoc explanations, refrain from disclosing negative aspects, or present responses that align with perceived social desirability [40]. Finally, in the present research, the data only include adults over 18 years of age. A large bulk of visits to primary healthcare is made by parents with small children. It is a limitation that our data do not include these consultations. Future research might also explore the triad of RN-child‒parent communication.

In conclusion, the PINPOINT project can contribute significantly to the development of clinically rooted methodologies for improving assessments and communication support by registered nurses in primary care (specific aim 5). To the best of our knowledge, this research will be the first-of-its kind to investigate practices of communication between patients and RNs and RNs’ decision-making to develop innovative and feasible solutions for successful and sustainable priority setting and to use a realist evaluation to examine its working mechanisms. To understand and help overcome challenges, this project will integrate an analysis of care needs and experiences as reported by patients with an analysis of communication during patient-RN visits and RNs’ experiences. Most likely, this research will contribute to knowledge that can strengthen RNs’ communication, assessments, and clinical decision-making in primary care. In the long term, this can contribute to how the competencies of different professionals are organized and carried out to make the best use of the resources within primary care service.

## Data Availability

The datasets generated and/or analyzed during the current study are not publicly available for ethical reasons but are available from the corresponding author upon reasonable request.

## List of abbreviations

AR: audio recordings
RN: registered nurse
VR-CoDES: the Verona Coding definition of emotional sequences
QUOTE-COMM: QUality Of care Through the patients’ Eyes
